### 10.4 Interim analysis (if applicable)

Not applicable, no interim analysis will be performed. However, in order to fuel the public debate, injury characteristics and specific treatment characteristics may be analyzed before follow-up is complete.

## 11. ETHICAL CONSIDERATIONS

### 11.1 Regulation statement

The study will be conducted according to the principles of the Declaration of Helsinki (64th World Medical Association General Assembly, Fortaleza, Brazil, October 2013). This study has been exempted by the medical research ethics committee (MREC); in Dutch: Medisch Ethische Toetsings Commissie (METC). Following review of the protocol, the MREC concluded that this study is not subject to the Medical Research Involving Human Subjects Act (WMO). They concluded that the study is a medical/scientific research, but no patients are subjected to procedures or are required to follow rules of behavior.

### 11.2 Recruitment and consent

Eligible persons with fireworks-related injuries (or the parents of pediatric patients) will be informed about the study as soon as possible after hospital presentation. They may receive the information at the ED/ward or at home. The local staff will ask permission to send contact details to the research team. Upon receipt of that permission, a local contact person in the participating hospital will provide details of the patient to the research team. The coordinating investigator or research assistant will send the patient (or parents) the information brochure. The coordinating investigator or a research assistant will visit the patient at the ward/outpatient clinic or at home within two weeks after presentation, in order to further explain the study, answer any questions the patient (or parents) may have, and for signing informed consent. This gives patients up to two weeks to consider their participation. Should patients decline participation only due to the burden of the questionnaires, consent will be asked to only use the information registered in the medical files.

Participation in this study is on a voluntary basis. If persons do not wish to participate, they can do so without specifying why. Deciding not to participate in the study will not affect regular treatment and follow-up care. Participants are allowed to withdraw from the study at any time after they have given their written consent.

Participation in this study will not have any influence on treatment. The General Practitioner (GP) will be informed about the participation of his/her patient.

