### 4.2 Inclusion criteria

In order to be eligible to participate in this study, a subject must meet all of the following criteria:

- 1) Patients with any injury caused by fireworks treated\* in a hospital in the Trauma Region Southwest Netherlands between December 1, 2017 and January 31, 2018
- 2) Provision of informed consent

\* Treatment is defined as any intervention for which  $\geq 1$  clinical follow-up visit is scheduled

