### 4.4 Sample size calculation

A report from VeiligheidNL mentions 574 patients during the annual change of year in 2014-2015 in The Netherlands. With 2 full months for inclusion we expect to increase this by at least 10% ( $n=638$ ). The Southwest Netherlands area contains 10 of the 90 Dutch hospitals. This could project to a possible sample of 70-80 patients. A formal sample size calculation for this observational study is not constructive. By including all patients treated in the Trauma Region Southwest Netherlands during the specific time interval, the largest possible sample will be enrolled. The larger the number of patients, the more reliable the analysis will be. Enrolling all patients possible will result in the highest reliability of data (*i.e.*, accurate point estimate with lowest possible variance).

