## 8. METHODS

### 8.1 Study parameters/endpoints

#### 8.1.1 Main study parameter/endpoint

The primary outcome measures are the **injury characteristics**. The following variables will be collected:

- Number of injuries
- Body site injured
  - 1) Head/neck (scalp, forehead, orbital, nose, cheek, mouth/lips, chin, ear, or neck)
  - 2) Eye
  - 3) Upper extremity (shoulder, upper arm, elbow, lower arm, wrist, hand palm, hand dorsum, thumb/first webspace, digit 2, 3, 4, 5, or other (text))
  - 4) Lower extremity (hip, upper leg, knee, lower leg, ankle, foot, other (text))
  - 5) Trunk (chest, abdomen, back, pelvis, or other (text))
  - 6) Other (text)
- Injured side (left, right, or not applicable)
- Type of injury per site (including text description)
  - 1) Burn (total body surface area (TBSA) and degree)
  - 2) Globe rupture (open or closed)
  - 3) Intra-ocular foreign body
  - 4) Penetration/perforation
  - 5) Corneal/adnex burn (chemical or thermic)
  - 6) Lens injury
  - 7) Retina injury
  - 8) Choroidal injury
  - 9) Corneal rupture
  - 10) Soft tissue damage (superficial or deep)
  - 11) Fracture/dislocation (fracture location)
  - 12) Amputation (level of amputation))
  - 13) Vascular damage (affected vessel)
  - 14) Neurological damage (affected nerve)
  - 15) Tendon damage (affected tendon)
  - 16) Other (text)

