#### B: Data collection

Patients will be followed for one year, with the first visit for baseline measurement planned as soon as possible, preferably within two weeks. Follow-up visits are planned at three months (window 2-4 months), six months (5-7 months), and 12 months (window 12-14 months) after presentation.. In case of early discharge from clinical treatment/follow-up, subsequent follow-up can be performed by visiting patients at home.

The study will not interfere with treatment or follow-up. Data concerning patient characteristics, injury characteristics, treatment details, and clinical outcome data will be extracted from the patient file as much as possible. These data will be collected from the patient's medical files as soon as possible after signing informed consent. For the purpose of the study, additional details concerning treatment and outcome (see paragraph 8) that are not mentioned in the patient's hospital files, will be registered on the case report forms directly. This will be done at the follow-up visits.

As soon as possible and within two weeks after inclusion patients will be asked to complete the questionnaire's, reflecting their pre-injury health status. For all participants this will be the EQ-5D-3L questionnaire. For patients with eye trauma the HUI-3 (domain vision), for patients with upper extremity trauma the HUI-3 (domain dexterity), the *Quick-DASH*, and CISS, for patients with lower extremity trauma the LEFS, and for patients with burn wounds the POSAS. At three, six and 12 months, treatment characteristics, health care consumption details and patient reported outcomes will be collected.

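### Section 11.2 offers file-only consent only to patients who decline solely because of the questionnaires, so other decliners are lost from a primary outcome taken mainly from the patient file

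*Protocol*

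**What the plan says.** Section 11.2 sets two levels of consent. Full participation comes first. The reduced level, use of the medical record alone, is tied to one reason for refusal: "Should patients decline participation only due to the burden of the questionnaires, consent will be asked to only use the information registered". The next paragraph of 11.2 says of refusal in general: "If persons do not wish to participate, they can do so without specifying why". The protocol describes no file-only route for anyone else.

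Other sections show what follows from not being asked:

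- Section 4.2 lists "Provision of informed consent" among the inclusion criteria.
- Section 8.1.1: "The primary outcome measures are the injury characteristics".
- Section 8.3, part B, says that patient, injury, treatment and clinical outcome data "will be extracted from the patient file as much as possible". It adds: "These data will be collected from the patient's medical files as soon as possible after signing informed consent".
- Section 4.4 rests the reliability of the study on completeness: "By including all patients treated in the Trauma Region Southwest Netherlands during the specific time interval, the largest possible sample will be enrolled".
- Section 10.3 plans to compare participants and non-participants on gender, injury location and age.

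**The concern.** The protocol accepts that a patient who will not complete questionnaires can still supply the primary data, and it creates a route for this. It then makes the route depend on a reason that nobody has to give. The word *only* in the condition also shuts out a patient who names the questionnaires together with something else. Other parts of the study could put a patient off, for example contact with the research team over a year, a home visit, or the scar examination for burn wounds. The protocol does not list these as reasons for refusal. They show that reasons other than the questionnaires are possible.

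Two things are at stake. The first is loss of primary data from patients who might have agreed to file use, in a study expecting only 70-80 patients. The second is selection: if those not asked differ from those enrolled, the reported injury percentages shift.

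**Working it through.** **Step 1: follow each kind of decliner through the text.**

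| Patient declines full participation | Asked for file-only consent (11.2)? | In the primary outcome (4.2, 8.3 B)? |
|---|---|---|
| solely because of the questionnaires | yes | yes, if the patient agrees |
| because of the questionnaires and something else | not provided for | no |
| for another reason | not provided for | no |
| without giving a reason | not provided for | no |

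Only the first row has a route. This result needs no figures.

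**Step 2: reproduce the protocol's expected sample (4.4).**

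- National count with the longer window: 574 / (1 - 0.10) = 637.8, rounded up to the stated 638. A literal 10% increase gives 574 x 1.10 = 631.4.
- Regional share: 638 x 10/90 = 70.9, or 631.4 x 10/90 = 70.2. Both lie at the lower end of the stated 70-80.

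**Step 3: range for the number of patients recoverable by a wider offer.** The protocol gives no refusal rate, no split of reasons and no acceptance rate. All three ranges below are assumptions.

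- N, eligible patients: 70-80 (4.4)
- r, share declining: 10-40% (assumed)
- s, share of decliners with no reason or another reason: 25-75% (assumed)
- a, share of those who would allow file use: 25-75% (assumed)

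Recoverable = N x r x s x a.

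- Lowest: 70 x 0.10 x 0.25 x 0.25 = 0.4
- With s = a = 50% and r = 10%: 70 x 0.10 x 0.25 = 1.8, and 80 x 0.10 x 0.25 = 2.0
- With s = a = 50% and r = 40%: 70 x 0.40 x 0.25 = 7.0, and 80 x 0.40 x 0.25 = 8.0
- Highest: 80 x 0.40 x 0.75 x 0.75 = 18.0

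**Step 4: what such a loss does to a reported percentage.** Let L be the recoverable patients as a share of all who would be enrolled under the wider offer. Then

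shift = L x (percentage in those retained - percentage in those lost).

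- L = 5%, difference 20 points: 0.05 x 20 = 1 point
- L = 20%, difference 30 points: 0.20 x 30 = 6 points

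The differences are illustrative. The protocol gives none, and no direction.

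**Step 5: precision.** The 95% half-width for a proportion of 50% is 1.96 x sqrt(0.25/n): 11.7 points at n = 70 and 12.7 points at n = 60. Losing ten patients costs about one point, so selection matters more than precision.

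**The case against.** The strongest reply is that nothing in 11.2 is contradictory. Patients who need not give a reason may still volunteer one, the consent talk is face to face, and the text names one case for the offer without forbidding it in others. The trigger also fits the protocol's own view of burden: 11.4 mentions no inconvenience beyond the questionnaires. This stands in part. A reader might infer that the two sentences of 11.2 contradict each other; they do not. The weakness is a rule that depends on information the study has no right to require. A team that follows the text has no instruction to ask the other decliners.

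A second reply is that the protocol expects non-participation and checks for it in 10.3, including on injury location, which is part of the primary outcome. This is correct and softens the point. The check leaves out the type and number of injuries, and detecting a difference does not bring back the data.

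A third reply is that the primary data are not wholly in the file. This is also correct. Section 8.3 says as much as possible, details missing from the file go on the case report form at follow-up visits, and Table 1 repeats injury characteristics at three months. File-only patients may therefore have some gaps. The protocol nevertheless treats file-only data as worth having.

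A fourth reply is that other filters also remove patients: permission to pass on contact details, unknown contact information, and language. These are separate, and the rule in 11.2 adds to them.

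**Conclusion.** The point holds as an inexpensive improvement to a stated rule. As written, 11.2 leaves patients who decline silently, or not solely because of the questionnaires, without a request for file use. Through 4.2 and 8.3 they are then absent from the primary outcome. This runs against the aim of 4.4 and may add selection that 10.3 can only partly reveal.

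The size is unknown. Under the assumed ranges, 0.4 to 18 of 70-80 patients could be recovered, so the loss may be negligible. A reader might infer that the injury profile will be distorted, for instance that severe injuries will be under-reported. The documents do not support this: they link refusal to no patient or injury characteristic, so neither the direction nor the amount of any shift can be stated. The finding rests on the wording of 11.2, 4.2 and 8.3 and does not depend on the figures.

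**What to change.** In 11.2, replace the condition with a general rule: at the consent contact, the research team asks every patient (or parent) who declines full participation whether the medical file alone may be used. No reason for declining is required, and the patient is free to refuse this too. In the report, give the numbers with full consent, file-only consent and no consent, next to the comparison planned in 10.3.

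The change widens a route that the protocol already has. It adds no visit, questionnaire or examination, and it gives local hospital staff no new consent task. The small downside is one extra voluntary question to people who have just declined.

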### 11.3 Objection by minors or incapacitated subjects (if applicable)

Pediatric patients are involved in this study. Should pediatric patients show any sign of objection, they will not undergo examination of scar tissue quality.

Adult patients will only be enrolled if they are able to provide informed consent themselves. They cannot be incapacitated.

#### **11.4 Benefits and risks assessment,**

Management (resuscitation, diagnostics, treatment, after-care, and follow-up visits) of study participants will not differ from those who do not participate. The study does not interfere with diagnostics, treatment, and follow-up at all. As part of this study, patients will be asked to complete questionnaires directly after inclusion (and within two weeks) and after three, six and after 12 months. Physical examination will be performed in patients with burn wounds to assess the scar quality at three, six and 12 months.

All clinical data will be collected during the follow-up visits as well as from the patients' medical files. Therefore, risks associated with participation can be considered negligible.

Participants should not expect any personal benefits from their participation in this study. Their participation may help future patients admitted with fireworks-related injuries. There are no other known additional risks involved in this study, aside from the slight inconvenience of completing the questionnaires. This will take approximately 30 minutes each time, including regular follow-up. The total time investment per patient is thus 90 minutes for three follow-up moments.

#### **Burden**

Adult patients and parents of pediatric patients are asked to complete the EQ-5D-3L (adult, youth or youth-proxy version). Depending their trauma patients have to complete injury-specific questionnaires. Patients with burn wounds will be subjected to physical examination regarding scar quality. The burden of completing the questionnaires and the physical examination can be considered as minimal.

#### **Group relatedness**

This study is group-related and cannot be conducted without the participation of pediatric patients. Gaining inside into the epidemiology of fireworks-related injuries, treatment, and outcome in pediatric patients can only be studied by enrolling those pediatric patients.

#### **11.5 Compensation for injury**

As the study is not subject to the Medical Research Involving Human Subjects Act (WMO), the statutory obligation to provide insurance for subjects participating in medical research (article 7 of the WMO) also does not apply.

**11.6 Incentives (if applicable)**

There is no incentive for patients to participate in this study. There are no costs involved for study participants. The motivation for the study is a potential benefit to all future patients admitted with fireworks-related injuries, as the results of this study will increase our knowledge on the epidemiology, costs and outcomes of fireworks-related injuries.

## 12. ADMINISTRATIVE ASPECTS, MONITORING AND PUBLICATION

### 12.1 Handling and storage of data and documents

Research data will be stored in a database (e.g., OpenClinica Clinical Trial Software for Electronic Data Capture or a similar platform that meets GCP standards and has an audit trail), and will be handled confidentially and anonymously. Research data that can be traced to individual persons can only be viewed by authorized personnel. These persons are the members of the research team, members of the health care inspection, and members of the Medical Research Ethics Committee of the participating hospital. Data review may be necessary in order to ensure the reliability and quality of the research. The handling of personal data is in compliance with the Dutch Data Protection Act (in Dutch: 'Wet Bescherming Persoonsgegevens', Wbp).

Research data will be stored under a code number that relates to individual persons. In order to trace data to an individual subject, a subject identification code list will be made to link the data to the subject. This code consists of the study acronym, three letters for the admitting hospital and three numbers for patient's study ID (e.g., ROCKET-EMC-001 for the first patient at Erasmus MC). Only the code number will be used for study documentation, annual progress reports and research publications. The principal investigator and research assistant are the only persons with the information linking individual persons to study code numbers. This data will be stored during the investigation and will be disposed of 15 years after completion of the study.

### 12.2 Monitoring and Quality Assurance

Any information on paper collected during this study will be placed in a research folder, which will be filed in locked cabinets in the research offices at Erasmus MC. Any electronic information collected during this study will be saved in a password-protected area. Only the study staff will have access to these data.

Patients will be asked for permission to store the informed consent, contact details, and CRFs at Erasmus MC, as the coordinating investigator or research assistant will contact patients during the study and will collect their follow-up data.

One of the project leaders or an independent person will monitor quality of the data by checking entry of data into the database. Data entry of injury details for a random selection of 25% of patients will be checked. In addition, data entry of questionnaires will be checked for 10% of all enrolled patients.

The questionnaires that patients and the coordinating investigator or research assistant complete during follow-up will be considered as source documents. With

respect to the clinical data such as surgical details, adverse events and interventions, the (electronic) patients files and case report forms will serve as source data.

### **12.3 Amendments**

Amendments are changes made to the research after a favorable opinion by the accredited MREC has been given. All amendments will be notified to the MREC that gave a favorable opinion.

Non-substantial amendments will not be notified to the accredited MREC, but will be recorded and filed by the sponsor. Examples of non-substantial amendments are typing errors and administrative changes like changes in names, telephone numbers and other contact details of involved persons mentioned in the submitted study documentation.

### **12.4 Annual progress report**

Not applicable, as this study will not be subject to the Medical Research Involving Human Subjects Act (WMO).

### **12.5 Temporary halt and (prematurely) end of study report**

No applicable, as this is not an intervention study.

Within one year after the end of the study (*i.e.*, completing data collection), the investigator will submit a final study report with the results of the study, including any publications/abstracts of the study, to the accredited MREC.

### **12.6 Public disclosure and publication policy**

Research data will be reported following the STrengthening the Reporting of OBservational studies in Epidemiology (STROBE) guidelines.

Research data can be presented or publicized in agreement with the principal investigator and project leaders only. Radiographs, CT images, and digital photographs will not be used for publication or teaching purposes without given consent by the patient. No research data that can be traced to individual persons will be presented or published.

The primary publication will be made by the principle investigator. Each participating hospital will provide one co-author for a collaborator group authorship (or full authorship if the journal allows it). This way, hospitals will be acknowledged for their participation.

This study will be registered at The Netherlands National Trial Register (NTR) (in Dutch; Nederlands Trial Register; [www.trialregister.nl](http://www.trialregister.nl)).

### 13. STRUCTURED RISK ANALYSIS

Not applicable, as this study does not involve an investigational or non-investigational product (see chapter 6 and 7).

#### 13.1 Potential issues of concern

Not applicable, as this study does not involve an investigational or non-investigational product.

a. Level of knowledge about mechanism of action

Not applicable.

b. Previous exposure of human beings with the test product(s) and/or products with a similar biological mechanism

Not applicable.

c. Can the primary or secondary mechanism be induced in animals and/or in ex-vivo human cell material?

Not applicable.

d. Selectivity of the mechanism to target tissue in animals and/or human beings

Not applicable.

e. Analysis of potential effect

Not applicable.

f. Pharmacokinetic considerations

Not applicable.

g. Study population

Not applicable.

h. Interaction with other products

Not applicable.

i. Predictability of effect

Not applicable.

j. Can effects be managed?

Not applicable.

#### 13.2 Synthesis

Not applicable, as this study does not involve an investigational or non-investigational product.

